## Abstract

**Introduction:**

Somali-born women comprise a large group of immigrant women of childbearing age in Sweden, with increased risks for perinatal morbidity and mortality and poor experiences of care, despite the goal of providing equitable healthcare for the entire population. Rethinking how care is provided may help to improve outcomes.

**Overall aim:**

To develop and test the acceptability, feasibility and immediate impacts of group antenatal care for Somali-born immigrant women, in an effort to improve experiences of antenatal care, knowledge about childbearing and the Swedish healthcare system, emotional well-being and ultimately, pregnancy outcomes. This protocol describes the rationale, planning and development of the study.

**Methods and analysis:**

An intervention development and feasibility study. Phase I includes needs assessment and development of contextual understanding using focus group discussions. In phase II, the intervention and evaluation tools, based on core values for quality care and person-centred care, are developed. Phase III includes the historically controlled evaluation in which relevant outcome measures are compared for women receiving individual care (2016–2018) and women receiving group antenatal care (2018–2019): care satisfaction (Migrant Friendly Maternity Care Questionnaire), emotional well-being (Edinburgh Postnatal Depression Scale), social support, childbirth fear, knowledge of Swedish maternity care, delivery outcomes. Phase IV includes the process evaluation, investigate process, feasibility and mechanisms of impact using field notes, observations, interviews and questionnaires. All phases are conducted in collaboration with a stakeholder reference group.

**Ethics and dissemination:**

The study is approved by the Regional Ethical Review Board, Stockholm, Sweden. Participants receive information about the study and their right to decline/withdraw without consequences. Consent is given prior to enrolment. Findings will be disseminated at antenatal care units, national/international conferences, through publications in peer-reviewed journals, seminars involving stakeholders, practitioners, community and via the project website. Participating women will receive a summary of results in their language.

Strengths and limitations of this studyThe feasibility design of the study together with the nested process evaluation will contribute valuable information for future controlled studies and in the design of antenatal care interventions that target inequalities in health between immigrants and non-immigrants.By emphasising dialogue, a person-centred approach and active participation of parents, midwives and bilingual research assistants throughout development and implementation, recruitment and retention are optimised and a relevant, pragmatic and acceptable model of care is likely to result.Funding has limited the scope of the study to two sites, with a focus on one group of immigrant women.

## Introduction

Sweden has a clearly stated goal of providing equitable healthcare for the whole population, which in recent decades has become increasingly diverse. Despite this, studies indicate that pregnancy outcomes among immigrant women are suboptimal compared with those of Swedish-born women.^1^ These health disparities point to the need for implementing and evaluating interventions to improve care for immigrant women and their families. This study protocol describes the development of an intervention to improve antenatal care (ANC) for Somali-born women and families giving birth in Sweden.

Somali-born women constitute one of the largest groups of immigrant women of childbearing age in Sweden^2^ after more than two decades of political instability in Somalia. Of all immigrant women, they are known to be at high risk of maternal and perinatal morbidity and mortality both in Sweden^3–5^ and internationally.^6^ The reasons are complex and include both premigration and postmigration factors. Insufficient healthcare provision and low socioeconomic conditions in the country of origin influence women’s health status.^7^ After migration to Sweden, later and lower attendance for antenatal care^8^ and poorer experiences of maternity care^9^ have been reported. Language difficulties and lack of familiarity with care systems and discrimination and suboptimal care are contributing factors.^3 10 11^ Furthermore, higher rates of anaemia, insufficient weight gain and infants born small for gestational age^8^ indicate that Somali women are not sufficiently reached by advice about prevention or treatment. Lower attendance at childbirth and parent education classes among immigrant women has also been found, with classes most often held in Swedish.^12^

Few measures have been taken in Sweden to reduce barriers to maternity care for immigrant women or to better meet their care needs. Furthermore, few studies have investigated how care might be designed in ways that are both attractive and acceptable to immigrant women and to midwives who are the main providers of care during pregnancy and childbirth. Respect, communication, community knowledge and care tailored to women’s circumstances and needs have been proposed as central components in quality maternity care.^13^ In line with this, a systematic review in five countries highlighted that immigrant women want the same things from care as non-immigrant women: care should be of high quality and safe, with adequate information and support and attentive to individual needs. The review also found however, that immigrant women consistently reported experiencing additional challenges, including communication difficulties, lack of familiarity with healthcare systems and discrimination.^10^

Language barriers, marginalisation and prevailing cultural stereotypes pose challenges in designing, implementing and evaluating innovative care models including, rather than excluding, immigrants. These factors need to be carefully addressed before widespread change of new models of care are introduced. Participatory approaches have shown promising results^14–16^ and reduce the risk of enhancing marginalisation. Focus on communication and meaningful dialogue throughout intervention design, recruitment, data collection, implementation and evaluation is valuable.^15^

In Sweden, the care of pregnant women during normal pregnancies is provided at community-based ANC clinics by registered midwives, based on national and regional guidelines.^17^ Included are 8–10 pregnancy check-ups free of charge, traditionally offered through individual appointments (30 min) with the same midwife throughout the pregnancy. Extra visits are booked and specialised medical referrals are made when needed. Parent education including preparation for childbirth and parenting is provided during the individual appointments or in groups/classes, mainly in Swedish and often focusing on first-time parents. Partners are encouraged to participate.

One innovative approach for improving antenatal care is group antenatal care (gANC). This care model incorporates pregnancy assessments and parent education in small groups, either with shorter individual appointments with the midwife at the beginning or end of the group session, or with individual clinical checks by the midwife provided in the group space,^18–20^ while the rest of the group can socialise. Self-assessments of blood pressure and urine have also been included in some gANC models.^18 20^ Results from studies in the USA, Iran and Sweden report improved satisfaction with care,^19 21–24^ improved iron taking, higher birth weight, lower caesarean section rates, more breastfeeding and earlier diagnosis of complications.^23^ Higher self-esteem and lower levels of stress, social conflicts and depression have been reported, as have more visits to ANC by fathers-to-be, increased support in social contacts with other parents and reduced costs,^18 19 21 23 25–27^ despite more time spent with the midwife throughout pregnancy. gANC thus appears to enhance women’s agency, dialogue, time with the midwife and social interaction, and to improve women’s views of their care and also some of their pregnancy outcomes. gANC may be especially valuable for specific groups of women, as seen for example in studies among young African-American women in the USA^21 28^ and among Karen refugee women in Australia.^15^

The Hooyo Project (‘mother’ in Somali) is a gANC initiative developed in Sweden in response to the evidence about lack of equity in pregnancy care provision and poorer outcomes for Somali-born women. gANC has not been evaluated among immigrant women and families in Sweden, yet it may well be a model of care that can break down cultural and care barriers, enable better dialogue and understanding between caregivers and immigrant women and improve women’s satisfaction with their care, especially if language support is provided.^15^

The overall aim for this study is to develop and test the acceptability and immediate impacts of gANC for Somali women residing in Sweden in an effort to improve experiences of antenatal care, knowledge about childbearing and the Swedish healthcare system, emotional well-being and ultimately, pregnancy outcomes.

Specific objectives include:

To establish with Somali-born women and antenatal caregivers the acceptability and feasibility of gANC and to develop an appropriate model to improve outcomes (phases I and II).To establish appropriate recruitment and data collection procedures and outcome measures in consultation with the Somali community and with care providers to evaluate the new model (phase II).To implement and evaluate an agreed model of gANC in partnership with the Somali community and antenatal caregivers (phases III and IV).

## Methods and analysis

### Design

An intervention development and feasibility study including focus group discussions, a historically controlled evaluation and process evaluation.^29 30^ The intervention is implemented in two antenatal care clinics in mid-Sweden. The feasibility and piloting includes testing procedures for acceptability, estimating the likely rates of recruitment and retention of women and the calculation of appropriate sample sizes for future controlled trials. Complex interventions that are adjusted to local, specific^31^ or personal needs^32^ are likely to be more effective than completely standardised models.^29^ Key principles underpinning the study are therefore:

Active involvement of Somali parents and midwives in needs assessment and care design.Attention to language and contextual factors.Flexibility in study methods to respond to issues as they arise.A care model ready to continue or be replicated after the project concludes with only minor adjustments.

Hooyo consists of four phases with process evaluation activities informing study progress. Phase I is the preparation phase, including needs assessment, the development of contextual understanding and building a logic model for the project. Phase II includes the development of the intervention and of the evaluation tools, and phase III involves implementation and evaluation of the intervention using historical controls. In phase IV, the implementation process, the feasibility and the mechanisms of impact are evaluated, including contextual factors, using Moore’s Process Evaluation of Complex Interventions as an overarching framework.^30^ Phases I and II were conducted in 2016–2017. Recruitment and data collection for the historically controlled evaluation (phase III) and process evaluation (phase IV) commenced in late 2016 and will be completed during 2020. Women in the control group were recruited between October 2016 and April 2018 and recruitment of women into the intervention began in May 2018 and will be complete in December 2019. Final data collection will be completed by July 2020. The paper covers methodological aspects of all four phases of the study.

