#### The intervention: gANC

The intervention consists of gANC offered at both sites, modified to the needs in each site and group. Women are allocated to a group with women at similar stages of pregnancy within a 4-week gestational age span. From the second visit (gestational weeks 20–26), they receive gANC. Each group will consist of six to eight women and partners (or another support person) for optimal group dynamics and dialogue. While reports of gANC internationally involve numbers in groups of 5–20 in low-income to middle-income countries^41^ and 8–12 in high-income countries,^42^ the need to provide interpreting during groups sessions led to the choice of a somewhat smaller group size as being appropriate to allow all group members a chance to participate in the discussions. Partners are generally encouraged to participate in Swedish ANC, and hence this will be the point of departure also for the gANC but with the final decision about partner participation taken by the women included in each group. Frequency and number of sessions follow the national Swedish programme for antenatal care, that is, eight to nine appointments during a normal pregnancy. Each visit includes a group session for 1 hour, facilitated by one of two midwives assigned to the group and with interpreter assistance. Although each group session has a focus on a theme related to pregnancy, birth or parenting in line with national recommendations,^17^ particular emphasis will be given to issues and questions raised by the participants. Group care allows women to talk with each other and share their experiences in their own language. They also hear midwives’ responses to other women’s questions, expanding the dialogue and information sharing that can occur between midwives and women. The presence of an interpreter facilitates communication between the women and the midwives.

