### Phase III: design and methods for the historically controlled evaluation of the intervention

#### Participants and recruitment

At both sites, primiparous and multiparous Somali-born women are recruited to the study. Recruitment and retention of participants to clinical studies is a well-documented challenge in research across languages and cultures.^49^ We therefore thoroughly planned how to optimise the recruitment and information processes in relation to eligible women and adjusted processes to local prerequisites at both sites. The Somali-speaking research assistant is based at site 1 where most needed and where the majority of the recruitment is performed. In site 2, team member MA is involved with recruitment, information and data collection, supported by the Somali-speaking research assistant form site 1. All pregnant Somali-born women attending the two ANC clinics receive brief information about the study from the midwives during their first visit, and if they agree to receive further information, they are then contacted by the research assistant or MA after the first ANC visit, either by telephone or face to face for further oral and written information in Somali, English or Swedish, as needed.

Inclusion criteria are being born in Somalia and <25 weeks of gestation. Exclusion criterion is a health condition preventing participation in group antenatal care, that is, severe mental health condition or if the pregnancy care were to be transferred to a specialist obstetric clinic. During the first 18 months of the study, recruited women were included in the control group receiving standard individual care, and in the following 18 months, women are included in the intervention group. All women are informed verbally and orally about the purpose of the study and that participation is voluntary. Women included in the control group were informed that their perspectives about their care would contribute knowledge valuable for a proposed intervention study aimed at improving antenatal care for migrant women.

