#### Data collection for the intervention

##### Questionnaires

Questionnaire data are collected at three time points (Q1, Q2, Q3). The baseline measurement (Q1) is conducted after recruitment, that is, before gestational week 25. Women are contacted for a face-to-face or telephone structured interview in Somali, Swedish or English at a place of their choice. Q1 includes questions on background (parity, education, income, occupation), migration (time of residence, reason for migration, migration status, language) and social support, psychological and physical well-being, knowledge of danger signs and the health system and expectations about the upcoming birth. Data for Q2 are collected in late pregnancy, after gestational week 35, in the same manner. Q2 includes questions on experiences of care and information during the ongoing pregnancy, knowledge of the health system, pregnancy and birth, social support and psychological and physical well-being and expectations for the upcoming birth. Q3 is administered 2 months postpartum and includes questions regarding the overall experience of pregnancy, ANC, birth and psychological and physical well-being. After each interview, a small gift is offered as a token of appreciation for women’s participation.

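### Intervention recruitment to December 2019 does not fit data collection ending by July 2020: late-recruited early bookers would have the 2-month postpartum questionnaire due after closing

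*Protocol article*

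**What the plan says.** All statements are in the protocol article.

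- **Design:** "recruitment of women into the intervention began in May 2018 and will be complete in December 2019". Two further statements cover the end of the study. Phases III and IV "commenced in late 2016 and will be completed during 2020", and, more specifically, "Final data collection will be completed by July 2020". Control recruitment ran from October 2016 to April 2018.
- **Participants and recruitment:** "Inclusion criteria are being born in Somalia and <25 weeks of gestation", with no lower limit. Midwives mention the study at the first visit, and women who agree to hear more: "they are then contacted by the research assistant or MA after the first ANC visit". The length of intake is given as 18 months for controls, and "in the following 18 months, women are included in the intervention group".
- **The intervention: gANC:** "From the second visit (gestational weeks 20–26), they receive gANC".
- **Questionnaires (data collection):** "Q3 is administered 2 months postpartum". Q2 is taken in late pregnancy, after week 35.
- **Sample size issues:** 100 women per group are expected. The number required is 174, which allows for 20% loss at the 2-month postpartum contact.

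**The concern.** A woman recruited in early pregnancy in late 2019 gives birth in the summer of 2020 and is due for Q3 in August to October, after the stated end of data collection. Three things make this worth correcting.

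- Q3 is the contact on which the attrition allowance rests. It covers the overall experience of antenatal care and psychological well-being, the domains of both primary outcomes. It is also where women's views on the content, structure and feasibility of group care are collected.
- Retention is one of the quantities the feasibility study is meant to estimate. Interviews missed only because the calendar ran out would understate retention under group care if they were counted as dropout.
- The loss would be one-sided. Control intake ended in April 2018, so no control is affected. Within the last weeks of intervention intake, the women affected are those who booked earliest, a trait tied to care-seeking. The comparison is already non-randomised.

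**Working it through.** **Inputs from the article:** intervention intake 1 May 2018 to 31 December 2019 (610 days, 20 calendar months); recruitment under 25 weeks; Q3 at birth plus 2 months; data collection ending by July 2020.

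**Assumptions:** birth at 40 weeks; closing on 31 July 2020 (generous) or 1 July (strict); even accrual of 100 women; one common gestation at recruitment. The article does not give the distribution of gestation at booking, so a range is shown.

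**The plan's own figure first.** 70 per group with 20% loss: 2 × 70 / 0.8 = 175. The stated 174 is 87 per group, and 87 × 0.8 = 69.6, so it reproduces to rounding.

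**Step 1: gestation needed at recruitment.** Q3 date = recruitment date + (40 weeks − gestation) + 2 months. For Q3 by 31 July 2020, birth must occur by 31 May 2020. Subtracting 280 days puts the start of the pregnancy (week 0) at 25 August 2019 or earlier.

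- Recruited 1 December 2019: 98 days / 7 = 14.0 weeks needed.
- Recruited 31 December 2019: 128 / 7 = 18.3 weeks needed (15.3 if birth is at 37 weeks, 20.3 if at 42).
- With a 1 July closing, the two limits are 18.3 and 22.6 weeks.

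**Step 2: Q3 date for recruitment on 31 December 2019.** At 8 weeks, 11 October 2020; at 10 weeks, 28 September; at 12 weeks, 14 September; at 20 weeks, 19 July; at 24 weeks 6 days, 15 June.

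**Step 3: number affected.** Share = days from the last feasible recruitment date to 31 December 2019, divided by 610.

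| Gestation at recruitment | Last feasible date, 31 July closing | Affected per 100 | Affected per 100, 1 July closing |
|---|---|---|---|
| 8 weeks | 20 Oct 2019 | 72/610 = 11.8 | 102/610 = 16.7 |
| 10 weeks | 3 Nov 2019 | 58/610 = 9.5 | 88/610 = 14.4 |
| 12 weeks | 17 Nov 2019 | 44/610 = 7.2 | 74/610 = 12.1 |
| 15 weeks | 8 Dec 2019 | 23/610 = 3.8 | 53/610 = 8.7 |
| 20 weeks | after intake ends | 0 | 18/610 = 3.0 |

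**Step 4: what remains obtainable by 31 July 2020.** A woman at 8 weeks on 31 December 2019 reaches week 35 after 27 weeks, on 7 July 2020, so Q2 can be taken. Birth falls after 31 July only for women below 9.6 weeks on 31 December. At a common 8 weeks, that is recruitment after 20 December: 11/610 = 1.8%.

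**Step 5: numbers against the target.** With 100 recruited and 12 affected, 88 remain, just above 87. With 17 affected, 83 remain, below it. If only 87 are recruited and 9.5% are affected (10 weeks), 87 × 0.905 × 0.8 = 63.0, below 70.

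**Step 6: the 18 months.** May 2018 plus 18 months ends in October 2019. Recruitment on 31 October at 9.6 weeks or later would meet 31 July. The control window, also called 18 months, spans 19 calendar months by the Design dates.

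**The case against.** The strongest defence is that July 2020 is a projected date in a condensed article and not a closing rule. The article nowhere says that women due later are dropped, and the Design section also allows completion at any time in 2020, which covers even October. A reader might infer that these women are certain to be lost. The documents do not support that. What remains is that the specific July date cannot be kept for everyone recruited up to December 2019.

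A second defence is that recruitment into the intervention could mean joining a group at weeks 20–26. Entry at 20 weeks on 31 December gives Q3 on 19 July, which just fits. But the Participants section places recruitment after the first visit, and the Design section speaks of recruiting controls, who join no group, in the same way. Even on this reading, birth at 42 weeks moves that Q3 to 2 August.

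A third is that the Introduction reports later antenatal attendance among Somali-born women, which points to the low end of the range. That is fair, and it is why the range must include 0.

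It is also tempting to treat the 18 months as proof that intake should have closed in October 2019. The same figure is used for a 19-month control window, so it looks rounded for both groups and does not settle which date is meant.

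**Conclusion.** The December 2019 and July 2020 dates conflict for women recruited late in the intake at an early gestation. The size depends on a booking gestation that the article does not give: about 12 down to 0 of 100 intervention women for gestations of 8 to 20 weeks with closing on 31 July, about 17 down to 3 with closing on 1 July, and no controls. This rests on even accrual and birth at 40 weeks.

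A reader might go further and conclude that birth outcomes and the primary comparison are compromised. The documents do not support that. With closing on 31 July, Q2, which covers care experience and psychological well-being, remains obtainable, and so do almost all births. The expected 100 per group also leaves some headroom over 87, though it is thin at the early-booking end and gone under a 1 July closing with everyone recruited at 8 weeks. This is a moderate timetable error that is cheap to correct. It does not undermine the design.

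**What to change.** Make the December 2019, 18-month and July 2020 statements agree. The better route is to keep December 2019 and state that Q3 and record retrieval end 2 months after the last participant's birth. For women recruited at 12 to 8 weeks on 31 December, that is about mid-September to mid-October 2020, still within the stated completion during 2020. State the recruitment period in months consistently with the dates.

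In the retention estimate, report any Q3 not obtained because of the closing date separately from loss to follow-up.

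The cost is about 2 to 3 more months of interviews by existing staff. Closing intake at the end of October 2019 instead would nearly remove the conflict, but it gives up 61 of 610 recruitment days, about 10 of 100 women under even accrual. That is roughly as many as the extension would save.
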